### 2.7. Quality Control

In order to guarantee the quality of the trial, it will be carried out under the supervision of two departments, Shanghai Municipal Hospital of Traditional Chinese Medicine and Shanghai Academy of Education Science. We will promptly input data on the ResMan website. The Clinical Research Center of Drugs of Shanghai University of TCM will work as the data monitoring team to identify problems in the project, examine collected data, and control bias. Meanwhile, a qualified clinical trial expert will be invited to monitor this study.

### 2.8. Statistical Analysis

All analyses will be performed on the Intention-to-Treat (ITT) population of participants who have at least one treatment. Data analyses will be performed with the use of the statistical software SPSS20.0. *t*-test is used to compare the measurement data between the two groups from the baseline to 4 weeks of follow-up; and rank-sum test is used for ranked data, while *χ*^2^ test is adopted to analyze categorical data. The significance level used for statistical analysis with 2-tailed testing was 5%. Data values are mainly presented as Mean ± SD.

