## Abstract

*Background*. Depression is frequently accompanied by sleep disturbances including insomnia. Insomnia may persist even after mood symptoms have been adequately treated. Acupuncture is considered to be beneficial to adjust the state of body and mind and restore the normal sleep-awake cycle. This trial is aimed at evaluating the efficacy and safety of electroacupuncture on treating insomnia in patients with depression.* Methods*. We describe a protocol for a randomized, single-blinded, sham controlled trial. Ninety eligible patients will be randomly assigned to one of 3 treatment groups: treatment group (acupuncture), control A group (superficial acupuncture at sham points), and control B group (sham acupuncture). All treatment will be given 3 times per week for 8 weeks. The primary outcome is the Pittsburgh Sleep Quality Index (PSQI). The secondary outcomes are sleep parameters recorded in the Actigraphy, Hamilton Rating Scale for Depression (HAMD), and Self-Rating Depression Scale (SDS). All adverse effects will be accessed by the Treatment Emergent Symptom Scale (TESS). Outcomes will be evaluated at baseline, 4 weeks after treatment, 8 weeks after treatment, and 4 weeks of follow-up.* Ethics*. This trial has been approved by the Ethics Committee of Shanghai Municipal Hospital of Traditional Chinese Medicine (2015SHL-KY-21) and is registered with ChiCTR-IIR-16008058.

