## 2. Methods/Design

### 2.1. Setting and Design

We will conduct a single-center, patient-assessor-blinded, randomized controlled trial to evaluate the efficacy and safety of electroacupuncture for insomnia in patients with depression. The trial will be performed at the acupuncture department in Shanghai Municipal Hospital of Traditional Chinese Medicine in Shanghai, China. We will recruit 90 patients who meet inclusion criteria and randomly assign them to one of 3 groups, receiving electroacupuncture, superficial acupuncture at sham acupoints, or sham acupuncture. After one week of washout period, patients will accept 12 weeks of observation (Table 1). All treatment will be given 3 times a week (every other day) for 8 weeks. Participants will be assessed at 4 time points, the baseline (1 week before treatment), the middle of the treatment (4 weeks after treatment starts), end of the treatment (8 weeks after treatment starts), and follow-up (4 weeks after treatment finishes). All participants will complete the assessments by the PSQI, Actigraphy, HAMD, SDS, and TESS. We will follow the Standards for Reporting Interventions in Clinical Trials of Acupuncture (STRICTA) [18] throughout the trial.

Figure 1 is a flowchart of the study.

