### 2.2. Sample Size Calculation

As a preliminary trial, the calculation of sample size is based on the open study about acupuncture for aging patients with depression and sleep disorders [20]. Referring to the study, the designer recruited 24 patients in each group to take acupuncture or sham treatment and also used PSQI as the main assessment indicator and suggested further study in controlled trials on the effects of acupuncture for younger patients with depression or insomnia. To study about the efficacy of electroacupuncture on depressive patients with insomnia, we positively take the previous results and 20% dropout rate into consideration and determine that the sample size of each group is 30 participants. With 1 : 1 : 1 allocation to each group, a total of 90 participants should be recruited.

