## 3. Discussion

Insomnia has been identified as the most common condition comorbid to depressive disorders [27]. The relationship between insomnia and mood symptoms is bidirectional in that poor sleep can precede an episode of major depressive disorder, and depressive mood can disrupt normal sleep patterns [4]. As research continues, some experts have suggested that comorbid insomnia and depression may have a different clinical course than either condition alone and may thus require specific treatment procedures. Electroacupuncture has been used as a complementary treatment to relieve unhealthy mood [28] and to normalize sleep disturbance [29] but the few studies focus on its efficacy and safety for treating comorbid depression and insomnia.

The main goal of our trial is to present a well-designed trial to study the therapeutic effect of EA on insomnia in depressive patients and overcome some methodological challenges in previous acupuncture clinical researches. Previous RCTs about acupuncture for depression or insomnia had limitations including imperfect blinding method, illogical design, or practical difficulty. To reach the goal, we design this strictly randomized controlled trial, setting two control groups to, respectively, apply sham acupoints and sham acupuncture method so that the result may help other researchers have better understanding about the effects of EA and the certain specificity of acupoints on treating insomnia and alleviating depression. In addition, we use single-blinded method to reduce test bias and ensure the reliability of the research.

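### A three-arm trial with three post-baseline PSQI visits is to be analysed by a two-group t-test at an unadjusted 5%, with no deciding pair or visit fixed

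*Protocol article*

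**What the plan says.** Section 2.1 describes a trial that will "randomly assign them to one of 3 groups, receiving electroacupuncture, superficial acupuncture at sham acupoints, or sham acupuncture". On timing, the same section says: "Participants will be assessed at 4 time points, the baseline (1 week before treatment), the middle of the treatment (4 weeks after treatment starts"), followed by the end of treatment at week 8 and a follow-up four weeks later. Table 1 marks PSQI at baseline and at each of the three later visits, with no visit singled out.

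The Abstract states: "The primary outcome is the Pittsburgh Sleep Quality Index (PSQI"). Section 2.6.1 describes the questionnaire and its 0–21 total, but gives no primary visit, change score or contrast.

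Section 2.8 gives one method for continuous data, a t-test that "is used to compare the measurement data between the two groups from the baseline to 4 weeks of follow-up". On the error rate it says only: "The significance level used for statistical analysis with 2-tailed testing was 5" per cent.

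The Discussion explains the two controls as "setting two control groups to, respectively, apply sham acupoints and sham acupuncture method". It ranks neither above the other.

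**The concern.** The analysis sentence refers to two groups without saying which two, and the trial has three. This goes beyond a detail held over for an analysis plan: the article states a test, a comparison and a significance level, and the comparison does not match its own design. The primary contrast and primary visit define the question the trial asks.

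As it stands, EA could be called effective on whichever control and whichever visit reached significance. A win over one control does not mean the same as a win over the other, because the Discussion gives the controls different purposes. If the choice is made after the data are seen, it cannot be credibly repaired.

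**Working it through.** **Inputs from the protocol article**
- Three arms, 1:1:1 (Sections 2.1, 2.2); three post-baseline PSQI visits (Section 2.1, Table 1).
- Two-sample t-test, two-sided 5%, no split or adjustment stated (Section 2.8).
- Group size (Section 2.2): the source study "the designer recruited 24 patients in each group to take acupuncture or sham treatment"; the plan then takes a "20% dropout rate into consideration and determine that the sample size of each group is 30 participants". The step reproduces: 24/(1 − 0.20) = 30 per group, and 3 × 30 = 90. Both 24 and 30 per arm are used below.

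The article states no familywise error rate, so there is no figure of its own to reproduce on that point.

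**Assumptions, not in the article**
- No true difference between any arms.
- Equal correlation ρ between a patient's PSQI scores at different visits, taken as 0.3 to 0.7.
- Any p<0.05, in either direction, counts as a positive result.

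**Step 1: benchmark.** For k independent tests at 5%, P(at least one p<0.05) = 1 − 0.95^k. This gives 9.8% for k=2, 14.3% for k=3, 26.5% for k=6, 37.0% for k=9 and 46.0% for k=12.

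**Step 2: allow for dependence.** The tests are not independent. Each arm mean has variance σ²/n, so each difference has variance 2σ²/n. EA versus A and EA versus B share the EA mean, so their covariance is σ²/n and their correlation is (σ²/n)/(2σ²/n) = 0.5. The same pair at two visits has correlation ρ. Both lower the rate below the benchmark, so it was simulated: 20,000 null trials per setting, t-tests at two-sided 5%. The Monte Carlo standard error near 22% is √(0.22 × 0.78/20,000) = 0.3 percentage points.

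P(at least one p<0.05), in per cent, for n=24 / n=30 per arm:

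| Tests counted | k | ρ=0.3 | ρ=0.5 | ρ=0.7 |
|---|---|---|---|---|
| EA vs each control, one visit | 2 | 8.9 / 9.0 | 9.4 / 9.3 | 8.9 / 9.1 |
| All three pairs, one visit | 3 | 11.8 / 12.9 | 12.1 / 12.4 | 12.4 / 12.3 |
| One pair, three visits | 3 | 13.9 / 13.7 | 12.7 / 12.3 | 11.0 / 11.1 |
| **EA vs each control, three visits** | **6** | **23.5 / 23.9** | **22.0 / 22.1** | **19.0 / 19.2** |
| All three pairs, three visits | 9 | 31.2 / 30.3 | 28.4 / 29.0 | 25.3 / 24.9 |
| All three pairs, baseline also tested | 12 | 38.2 / 38.7 | 34.4 / 34.7 | 29.6 / 29.5 |

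In the one-visit rows ρ plays no part, and differences across columns are simulation noise.

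**Step 3: sensitivity.** On change-from-baseline scores, the six EA-versus-control tests give about 22% and the nine tests 28–29%, whatever ρ is. On raw scores at ρ=0.9, the six tests fall to about 15% and the nine to about 20%.

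**Step 4: after a fix.** One named pair at one named visit gives 5%. Two named contrasts at one visit, tested in a fixed sequence or by Holm, hold the familywise rate at or below 5%.

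**The case against.** The strongest case against is that the article does not state the testing scheme that produces the larger figures. A reader might infer that Section 2.8, followed literally, prescribes nine t-tests (three pairs at three visits), so that the false-positive rate is 25–31%. The documents do not support that as a statement of fact. Section 2.8 gives no number of pairs or tests. Its time span could mean a test at every visit, or one comparison of change from baseline to follow-up. On the second reading the rate is about 9% with two pairs or 12% with three. No success rule is stated either: if EA had to beat both controls at one named visit, there would be no inflation. Control A versus control B also cannot support a claim that EA works, so the six-test family fits the harm better than the nine-test one. All of this stands.

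It can also be said that this is a condensed article, and that a full protocol or analysis plan not shown could contain an adjustment. That is fair, so the lack of a multiplicity method is not by itself the fault. What remains is that the published comparison does not fit three arms and the primary outcome has no deciding contrast or visit.

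Finally, the Background and Section 2.2 call the trial preliminary, and whether two controls with separate purposes need joint error control is debated. This softens the point without removing it. The Background also says the results will help show whether EA is effective and safe, and the Discussion expects more credible evidence than earlier trials gave.

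**Conclusion.** The point holds and should be fixed. It is certain from the text that Section 2.8 sets a two-group test against a three-arm design with three post-baseline PSQI visits, and that no section fixes the pair or visit that decides the trial.

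The size depends on the reading. The most relevant scenario, EA against each control at all three post-baseline visits with any p<0.05 taken as success, gives about 19–24% under no effect for ρ of 0.3–0.7. Across the multiple-test readings the range is about 9% (two pairs, one visit) to 25–31% (three pairs, three visits), and about 29–39% if baseline is tested as well. The correlation, the family of tests and the success rule are all assumptions. No single figure in this range is the trial's error rate, because the plan does not define one.

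**What to change.** In Sections 2.6.1 and 2.8:
- Name PSQI at one visit as the primary endpoint. Week 8, the end of treatment, is the natural choice.
- Replace the two-group wording with the named contrasts EA versus control A and EA versus control B.
- Hold familywise error at two-sided 5% over these two. One option is a fixed sequence, each test at 5% and the second made only if the first is significant. Nothing in the article ranks one control above the other, so the sponsor should set and justify the order before unblinding. Holm needs no order: the smaller p-value is compared with 2.5% and, if it passes, the larger with 5%.
- Label control A versus control B, and all PSQI tests at other visits, as supportive.

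The cost is a few lines of wording and no added patients. Significance at another visit or pair can no longer be claimed as primary success. Under a fixed sequence, neither can the second contrast if the first fails. Holm avoids that dependence on order but sets a stricter first threshold. The effect on power cannot be calculated, because Section 2.2 gives no effect size, standard deviation or power.

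### Section 2.8 compares PSQI by an unadjusted two-group t-test although baseline PSQI is collected on everyone; the test is valid but less precise than it need be

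*Protocol article*

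**What the plan says.** The Abstract names the primary outcome: "The primary outcome is the Pittsburgh Sleep Quality Index (PSQI"). Section 2.8 is the only analysis text. For continuous outcomes it says that a t-test "is used to compare the measurement data between the two groups". With the time span that follows, the clause reads "is used to compare the measurement data between the two groups from the baseline to 4 weeks of follow-up". It keeps rank-sum and chi-square tests for ranked and categorical data, and it names no covariate, regression or mixed model. Testing is two-sided at 5%.

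The baseline values are part of the design. Section 2.1 says "All participants will complete the assessments by the PSQI, Actigraphy, HAMD, SDS, and TESS", and the Abstract says "Outcomes will be evaluated at baseline, 4 weeks after treatment, 8 weeks after treatment, and 4 weeks of follow-up". Table 1 marks PSQI, actigraphy, HAMD and SDS at baseline, and section 2.1.1 requires a PSQI above 7 at entry, so every participant should have a pre-treatment PSQI.

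Section 2.4 uses simple randomisation without stratification. Section 2.2 refers to an open study in which "the designer recruited 24 patients in each group to take acupuncture or sham treatment", allows for 20% dropout and sets 30 per group.

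**The concern.** The stated test can be read in two ways, and neither makes the best use of the baseline.

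- **Follow-up scores at each visit.** Baseline is ignored, and part of any chance baseline difference between arms stays in the estimate.
- **Change from baseline.** Baseline is subtracted in full, as if the slope of follow-up on baseline were 1. When the true slope is smaller, this over-corrects and adds noise.

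ANCOVA estimates the slope from the data. With 24 to 30 patients analysed per arm the confidence intervals will be wide in any case, so variance that could be removed with data already in hand matters. The stake is the width of those intervals and the power of each comparison between arms. Because the article names the method, this is a stated choice and not a detail left to an analysis plan.

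**Working it through.** **Inputs**

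- From section 2.2: 24 per group in the earlier study, 20% dropout, 30 per group, 1:1:1.
- From section 2.8: two-sided 5%; analysis of everyone with at least one treatment.
- Assumed: 80% power, and r between 0.2 and 0.7. The article gives no effect size, SD, power or correlation, so differences are in units of the follow-up SD.

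**The plan's own figure.** 24/(1 − 0.20) = 30 per group, and 3 × 30 = 90. This reproduces. In reverse, 30 × 0.80 = 24 per arm. Because the analysis set is wider than completers, the number analysed may lie between 24 and 30, and both ends are shown.

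**Relative variance of the treatment difference.** Take the follow-up SD as 1 and the baseline SD as k.

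- t-test on follow-up scores: 1
- t-test on change scores: 1 + k² − 2kr, which is 2(1 − r) when k = 1
- ANCOVA: 1 − r²

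Since 1 + k² − 2kr = (1 − r²) + (k − r)², ANCOVA is no worse than a change score whatever k is. With k = 1 the ratio is (1 − r²)/[2(1 − r)] = (1 + r)/2. These formulas leave out the small cost of estimating the slope, so the gain at the lowest r is slightly flattering.

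| r (assumed) | ANCOVA vs follow-up score | ANCOVA vs change score, k = 1 |
|---|---|---|
| 0.2 | 0.96 | 0.60 |
| 0.3 | 0.91 | 0.65 |
| 0.5 | 0.75 | 0.75 |
| 0.7 | 0.51 | 0.85 |

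**Detectable difference for one comparison of two arms.** Noncentral t, with 2n − 2 degrees of freedom for the t-test and 2n − 3 for ANCOVA.

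| n per arm | r | t-test, follow-up score | t-test, change score (k = 1) | ANCOVA |
|---|---|---|---|---|
| 24 | 0.2 | 0.826 | 1.045 | 0.810 |
| 24 | 0.3 | 0.826 | 0.977 | 0.788 |
| 24 | 0.5 | 0.826 | 0.826 | 0.716 |
| 24 | 0.7 | 0.826 | 0.640 | 0.590 |
| 30 | 0.5 | 0.736 | 0.736 | 0.637 |

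At r = 0.5, ANCOVA with 24 per arm is worth 24/0.75 = 32 per arm without adjustment. For an assumed true difference of 0.8 SD at 24 per arm, power rises from 77% to 88%. At r = 0 the lost degree of freedom leaves power unchanged to three decimals (0.774).

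**Chance imbalance.** At 24 per arm the standard error of the baseline mean difference is √(2/24) = 0.29 SD. A follow-up-score t-test carries over a fraction r of any imbalance: at r = 0.5, a one-standard-error imbalance shifts the estimate by 0.5 × 0.29 = 0.14 SD. With k = 1, a change score carries (r − 1) times the imbalance, here 0.14 SD in the opposite direction.

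**The case against.** The strongest reply is that nothing here is wrong. A two-sample t-test in a randomised trial is unbiased, holds its type I error, and has a standard error that already allows for chance baseline imbalance. The article also calls the trial preliminary (Background and section 2.2). This stands: the point is about efficiency.

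Four further replies limit the size.

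- **The wording may mean change scores.** Baseline is then used, and the gain differs. A reader might take the r = 0.7 figures, a variance ratio of 0.51 and a fall from 0.83 to 0.59 SD, as the general gain. They hold only against a follow-up-score t-test. Against a change score at r = 0.7 the ratio is 0.85 and the fall is from 0.64 to 0.59 SD.
- **Equal variances are assumed in the change-score figures.** It is tempting to say that a change score is noisier than ignoring baseline whenever r is below 0.5. That needs k = 1; in general the threshold is k/2. The PSQI entry cut truncates baseline and not follow-up, so k may be below 1. For illustration, k = 0.7 and r = 0.3 give 1 + 0.49 − 0.42 = 1.07, against 1.40 with k = 1.
- **r is unknown and may be low.** The entry limits on PSQI (above 7) and HAMD (20 to 35) narrow the baseline range. Actigraphy is worn for one night at a time (section 2.3 and Discussion), and its correlation is equally unknown. Against a follow-up-score t-test at r = 0.2 the gain is only 4%.
- **24 per arm is not the defined analysis set.** With 30 the gain at r = 0.5 remains, from 0.74 to 0.64 SD.

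These replies reduce the claimed size. They do not remove the point, because ANCOVA has the smaller variance under either reading, apart from one degree of freedom.

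**Conclusion.** The point holds as a recommendation on precision. The stated t-test is valid but uses the baseline either not at all or with a fixed slope of 1. At r = 0.5, and at equal variances for the change-score reading, both readings give the same result: a quarter of the variance could be removed, and the detectable difference would fall from 0.83 to 0.72 SD at 24 per arm or from 0.74 to 0.64 SD at 30. Over r = 0.2 to 0.7 the reduction runs from 4% to 49% against follow-up scores, and from 40% down to 15% against change scores.

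Two stronger inferences are not supported. A reader might conclude that the planned test is biased or invalid; randomisation rules that out. A reader might also think that a baseline imbalance enters the estimate in full; only a fraction r of it does in a follow-up-score comparison. That the covariate is absent is certain from section 2.8. The size of the gain rests on an assumed r.

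**What to change.** In section 2.8, replace the t-test for PSQI, and likewise for HAMD, SDS and the actigraphy measures, by ANCOVA at each post-baseline time point with arm and that outcome's own baseline as covariate. A mixed model over the visits with the same baseline covariate would serve equally well. Report adjusted mean differences between arms with 95% confidence intervals. This also settles whether change or follow-up scores are meant: with the baseline as covariate, the ANCOVA treatment difference is the same for both.

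The cost is a rewording of section 2.8, one degree of freedom and a little programming in SPSS, the planned software. No new data are needed, and the sample size stays as it is.

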### 2.9. Ethics

The trial has been approved by the Ethics Committee of Shanghai Municipal Hospital of Traditional Chinese Medicine, Shanghai, China (2015SHL-KY-21) and is registered with Chinese Clinical Trials Registry (ChiCTR-IIR-16008058). All patients will sign the written informed consent before participating in the trial.

## 3. Discussion

Insomnia has been identified as the most common condition comorbid to depressive disorders [27]. The relationship between insomnia and mood symptoms is bidirectional in that poor sleep can precede an episode of major depressive disorder, and depressive mood can disrupt normal sleep patterns [4]. As research continues, some experts have suggested that comorbid insomnia and depression may have a different clinical course than either condition alone and may thus require specific treatment procedures. Electroacupuncture has been used as a complementary treatment to relieve unhealthy mood [28] and to normalize sleep disturbance [29] but the few studies focus on its efficacy and safety for treating comorbid depression and insomnia.

The main goal of our trial is to present a well-designed trial to study the therapeutic effect of EA on insomnia in depressive patients and overcome some methodological challenges in previous acupuncture clinical researches. Previous RCTs about acupuncture for depression or insomnia had limitations including imperfect blinding method, illogical design, or practical difficulty. To reach the goal, we design this strictly randomized controlled trial, setting two control groups to, respectively, apply sham acupoints and sham acupuncture method so that the result may help other researchers have better understanding about the effects of EA and the certain specificity of acupoints on treating insomnia and alleviating depression. In addition, we use single-blinded method to reduce test bias and ensure the reliability of the research.

Optimizing point selection of acupuncture treatment for insomnia is an important part in this trial. The TCM theory about the specificity of acupoints is one of the most mysterious questions mentioned by the worldwide acupuncture researchers [30]. To give some evidence for the effects of “specific” acupoints in treating depression related insomnia, we set two control groups with acupuncture at “nonspecific” acupoints in this trial, hoping to figure out differences between the two ways of acupoints selection. Combining acupuncture theory with acupuncturists' experience, we regard acupuncture method of regulating the Governor Vessel as the main treatment principle and choose two acupoints (GV20 and GV29) in GV for electroacupuncture to enhance the curative effect for treating insomnia. Imageology study also found that electroacupuncture stimulation at GV20 can modulate the default mode network in patients with depressive disorder, which supports that EA has positive effect on treating comorbid depression and insomnia [31]. The application of the Actigraphy is another flashpoint in the trial. Studies reported that the wrist-worn sleep monitor provides more objective data of sleep quality and duration than patients' self-reported data [32]. It is helpful to compare, analyze, judge, and evaluate changes in sleep quality before, during, and after the treatment. We ask the participants to wear the Actigraphy at night each time we give it to them and to return it next day so that we can ensure the latest data and analyze them in time.

The key technical issues that need to be solved in this trial are (1) the application of the sham acupuncture method and (2) the challenge of patient compliance. All acupuncturists should accept training for several times before the trial begins to ensure the implementation of the sham acupuncture techniques and prepare for reasonable explanation in case of being questioned by patients in control B group. Patients' compliance is a common issue existing in various clinical trials. Good compliance is the central premise to help the trial move forward. Therefore, we will strengthen the publicity and education of medical knowledge to patients and improve healthcare in all aspects. For instance, appointments should be made by phone or email to establish the reservation system; reasonable arrangement of consultation time should be made to increase the patients' attendance rate; professional researchers will conduct family follow-up observation to supervise its implementation; and free acupuncture treatment will be promised by acupuncturists if the patients are not satisfied with the results of their treatment after the trial.

The limitation of this trial is the single-blinded method. Different from the placebo medicine trial, it is inevitable for the acupuncturists to know well about the real or sham acupuncture treatment and its possible effects. This is the reason why we apply the eye mask for the patients, use drape for separation during treatment, and set up training program for the acupuncturists.

We will standardize point selection, manipulation, needling instrument, and therapists' clinical experience in accordance with the STRICTA to ensure quality control of our acupuncture treatment. The objectively recognized assessment will improve the reliability of efficacy evaluation. We expect that this study will provide more credible evidence for the effects of EA on insomnia and depression and make up for the deficiencies in the current methodology of acupuncture clinical trials.

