#### 2.5.1. Treatment Group

Participants in the treatment group will receive electroacupuncture treatment. Acupuncture method of each acupoint is shown in Table 2. Regular acupuncture method will be applied at Baihui (GV20), Shenting (GV24), Yintang (GV29), bilateral Anmian (EX-HN22), Shenmen (HT7), Sanyinjiao (SP6), and Neiguan (PC6). After needle insertion, rotating manipulation or lifting-thrusting manipulation will be applied for “Deqi” sensation. The electroacupuncture apparatus (CMNS6-1, Wuxi Jiajian Medical Device Co., Ltd., China) will be connected to the needles at Baihui (GV20) and Yintang (GV29) for 30 minutes and deliver a continuous wave to the patients. The frequency will be set at about 30 Hz and the amplitude will be less than 20 V during the treatment, based on the endurance of each patient.

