#### 2.5.2. Control A Group

Participants in control A group will receive superficial acupuncture treatment at the following sham acupoints: bilateral acupoints 0.5 cun upper outer of Jiache (ST6), Waiguan (SJ5), Yangchi (SJ4), and Xuanzhong (GB39); acupoint upper outer of Quanliao (SI18); and bilateral acupoints in the middle of Tianyou (SJ16) and Tianrong (SI17). Acupuncturists will do no manipulation at each acupoint after inserting the needles. The electroacupuncture apparatus will be connected to the needles at bilateral acupoints 0.5 cun upper outer of ST6, with zero frequency and amplitude.

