#### 2.5.3. Control B Group

Participants in control B group will receive sham acupuncture treatment at the same acupoints as control A group. The sham acupuncture will be applied with the placebo needles used in some trials before [22, 23]. When the tip of the blunt needles touches the skin, the patient will get a pricking sensation but there is no real needle inserted into the skin. The electroacupuncture apparatus will be set beside the patients, with no connection to the needles. Inform the patients when removing the needles after 30 minutes. Use the dry cotton ball to press the acupoints so that patients can feel the withdrawal of the “real” needles.

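### The two control groups are partly justified by acupoint specificity, but no pair of arms differs in acupoints alone, so no difference between arms can be attributed to the points

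*Protocol article*

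**What the plan says.** The rationale is in the Discussion (section 3). It says the design is "setting two control groups to, respectively, apply sham acupoints and sham acupuncture method", so that the result may help others to "have better understanding about the effects of EA and the certain specificity of acupoints on treating insomnia and alleviating depression". The following paragraph returns to the subject: it gives point selection a prominent place in the trial, notes that both controls are needled at nonspecific points, and says the investigators are "hoping to figure out differences between the two ways of acupoints selection".

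The arms are defined in section 2.5:

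- **Treatment group (2.5.1, Table 2).** Regular needling at the chosen points, to 0.5 or 1 cun. For Deqi, "rotating manipulation or lifting-thrusting manipulation will be applied". Current is delivered at about 30 Hz through two of the needles.
- **Control A (2.5.2).** Superficial needling at sham points. "Acupuncturists will do no manipulation at each acupoint after inserting the needles". The device is wired to two needles but has no output.
- **Control B (2.5.3).** Participants "will receive sham acupuncture treatment at the same acupoints as control A group". The needles are blunt and do not enter the skin. "The electroacupuncture apparatus will be set beside the patients, with no connection to the needles".

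**The concern.** The word *respectively* suggests that one control varies the points and the other varies the method, so that the two effects could be separated. The arm definitions do not do this. Control B has sham points as well as a sham method. No arm combines the chosen points with a sham method, and no arm gives active EA or regular manipulated needling at the sham points.

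At stake is how a positive result would be read. If EA does better than control A, a reader who takes the Discussion at its word could credit the choice of points, when current, depth or manipulation would explain the difference equally well. The only limitation the Discussion names is single blinding, so the reader is not warned about this confounding.

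**Working it through.** The article gives no figure for this point, so the check is to set out the arms and ask whether a point effect can be recovered from them.

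**Step 1. Components by arm** (sections 2.5.1 to 2.5.3 and Table 2).

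| Component | EA | Control A | Control B |
|---|---|---|---|
| Points | chosen | sham | same sham points as A |
| Insertion | regular, 0.5 or 1 cun | superficial | none |
| Manipulation for Deqi | yes | no | no |
| Current | about 30 Hz | zero | zero |
| Leads connected | yes | yes | no |

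**Step 2. Pairwise differences.**

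- EA vs A: points, depth, manipulation, current = 4 components.
- EA vs B: points, penetration, manipulation, current, lead connection = 5 components. Control B has no insertion, so depth and penetration are one difference here, not two.
- A vs B: penetration and lead connection = 2 components; the points are identical.

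Pairs that differ in points alone: 0 of 3.

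**Step 3. Estimability in an additive model.** Let p be the effect of the chosen points over the sham points, r the effect of regular insertion and s of superficial insertion (each against none), m of manipulation, c of current and l of lead connection. Then:

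- EA − A = p + (r − s) + m + c
- EA − B = p + r + m + c + l
- A − B = s + l

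The first and third lines add up to the second, so there are only two independent contrasts. With columns (intercept, p, r, s, m, c, l), the design rows are:

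- EA: (1, 1, 1, 0, 1, 1, 1)
- A: (1, 0, 0, 1, 0, 0, 1)
- B: (1, 0, 0, 0, 0, 0, 0)

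This matrix has rank 3. Adding the row that picks out p alone, (0, 1, 0, 0, 0, 0, 0), raises the rank to 4, so p is not estimable. The same can be seen by hand: only the EA row has entries in the p, m and c columns, so any combination that gives p weight 1 also gives m and c weight 1.

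**Step 4. Does sample size matter?** The plan's 30 per group agrees with inflating the reference study's 24 per group for 20% dropout (section 2.2): 24 / (1 − 0.20) = 30, and 3 × 30 = 90. That figure has no bearing here. More participants would estimate EA − A more precisely, but it would still be the sum p + (r − s) + m + c.

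**The case against.** The strongest reply is that the article promises little. Its language is tentative, and it speaks of helping understanding and of hope. The trial is called preliminary in the Background and in section 2.2. Specificity appears only in the Discussion: the aims in the Abstract, Background and section 2.1 concern the efficacy and safety of EA, and section 2.8 names no specificity test. All of this stands. A reader might infer that the plan undertakes to demonstrate acupoint specificity, or that its authors will publish a positive result as proof of it. The documents support neither. Specificity is nevertheless a stated reason for the control structure, and the arms cannot separate points from current, depth and manipulation even at the modest level hoped for.

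A second reply is that *respectively* is merely loose, since section 2.5.3 is open about control B using control A's points and the Discussion itself says both controls use nonspecific points. It is true that the arms are not concealed. The sentence still describes a separation that they do not provide.

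A third reply is that the data would not be wholly silent about the points. If depth, manipulation and current are assumed to do no harm and effects add, then (r − s) + m + c is at least zero and EA − A is an upper bound on p. A precise difference near zero would then argue against a large point effect. That is correct under those assumptions, which the article does not state. It is why the point should not be stretched to say that no result could ever bear on the points. What fails is attribution of a difference to them.

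The full protocol or an analysis plan could not repair this. The issue is not a missing detail: the aim and the arms are both stated, and no analysis makes p estimable from these three arms.

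**Conclusion.** The concern holds, within limits. None of the three contrasts isolates the acupoints: EA differs from control A in 4 components and from control B in 5, and the two controls share the same points. An EA-control difference therefore cannot be attributed to point selection, and the Discussion's account of the two controls does not fit section 2.5.3.

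The component list is read directly from the arm definitions. The formal non-estimability result assumes additive effects; allowing interactions would add unknowns and would not help.

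A reader might go further and infer that the trial cannot answer its main question. It can: both EA-control contrasts remain valid comparisons of the whole EA package with a sham package, and nothing in this point touches that.

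**What to change.** Change the wording of the Discussion, and carry the same statement into the analysis plan:

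1. Remove the acupoint-specificity aim, or limit it to a motivation that this trial does not test.
2. Replace *respectively* with a description that matches section 2.5.3: both controls use the same sham points, one with superficial needling and the other with non-penetrating needles.
3. State in advance that EA vs A and EA vs B each estimate the effect of the whole EA package against that sham package, and that A vs B is exploratory and reflects penetration together with the dummy lead connection.
4. State that no difference between arms will be attributed to point specificity.

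The arms, procedures, sample size and tests stay as they are. The cost is a few sentences and the loss of one hoped-for secondary conclusion.
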